#### **F. Gender/Minority/Pediatric Inclusion for Research**

All efforts will be made to ensure that our participant population closely resembles the ethnic and racial composition of the greater Tulsa area. Women and minorities will be included in the study without prejudice according to their representation in the study population. Adult subjects will be recruited from the greater Metro Tulsa area and should thus share the racial and ethnic composition of this area. Adolescents aged 15 and up will be included in the study. We include adolescents for these reasons: 1) several forms of brain maturation occur during adolescence. Primary among them in females is the onset of menorrhea. Menstrual cycle onset requires hypothalamic-pituitary-adrenal

(HPA) axis engagement of ovarian and uterine responses and is complete in the general US population by age 15. 2) While the mean age at onset of AN is 18.5 +/- 5.1 years, there is substantial variability and age at onset has continued to decrease (Favaro et al, 2009 *J Clin Psychiatry*). Excluding AN adolescents would therefore miss a substantial portion of the age at onset for the AN population. 3) Prefrontal myelination is an additional brain maturation phase but since this is not complete until the late 20s, we did not feel this developmental phase of prefrontal cortex maturation was an acceptable decision criterion for inclusion.

### Time and Events Table for Study

| Procedures                                                          | Screening Enrollment Visit 1 | Visit 2 (e.g. empty stomach) | Visit 3 (Gastric Mapping) | 1-month Follow-Up Visit 4 | 3-month Follow-Up Visit 5 c | 6-month Follow-Up Visit 6 c |
|---------------------------------------------------------------------|------------------------------|------------------------------|---------------------------|---------------------------|----------------------------------------|----------------------------------------|
| Informed consent                                                    | X                            |                              |                           |                           |                                        |                                        |
| Demographics                                                        | X                            |                              |                           |                           |                                        |                                        |
| Medical history                                                     | X                            |                              |                           |                           |                                        |                                        |
| Current medications and interim medical procedures                  | X                            | X                            |                           | X                         | X                                      | X                                      |
| Vital Signs                                                         | X                            | X h               |                           |                           |                                        |                                        |
| Height                                                              | X                            |                              |                           | X d            | X d                         | X d                         |
| Weight                                                              | X                            |                              |                           | X d            | X d                         | X d                         |
| Urine, drug & pregnancy screen a                         | X                            | X                            |                           |                           |                                        |                                        |
| Breathalyzer Test                                                   | X                            | X                            |                           |                           |                                        |                                        |
| Childhood Trauma Questionnaire                                      | X                            |                              |                           |                           |                                        |                                        |
| Randomization                                                       | X                            |                              |                           |                           |                                        |                                        |
| Stop Signal and Tone Tasks                                          |                              | X                            |                           |                           |                                        |                                        |
| Administer assigned intervention: capsule stimulation               |                              | X                            |                           |                           |                                        |                                        |
| State Trait Anxiety Inventory pre/post intervention                 | X b               | X i               |                           | X b            | X b                         | X b                         |
| PANAS-X pre/post intervention                                       | X                            | X                            |                           | X                         | X                                      | X                                      |
| Interceptive ratings                                                | X                            | X                            |                           |                           |                                        |                                        |
| Anxiety Sensitivity Index-3 pre/post intervention                   | X                            | X                            |                           | X                         | X                                      | X                                      |
| PHQ-9                                                               | X                            |                              |                           | X                         | X                                      | X                                      |
| IDAS-II Questionnaire                                               | X                            |                              |                           | X                         | X                                      | X                                      |
| NIH PROMIS Anxiety Scales                                           | X                            |                              |                           | X                         | X                                      | X                                      |
| Sheehan Disability Scale                                            | X                            |                              |                           | X                         | X                                      | X                                      |
| Yale-Brown EDS Self-Report (ED YBOCS SRQ)                           | X                            |                              |                           |                           |                                        |                                        |
| Big Five Inventory (BFI)                                            | X                            |                              |                           |                           |                                        |                                        |
| Reward Punishment Sensitivity                                       | X                            |                              |                           | X                         | X                                      | X                                      |
| MAIA Questionnaire                                                  | X                            |                              |                           | X                         | X                                      | X                                      |
| Body Scales (Somatomap)                                             | X                            | X                            | X                         |                           |                                        |                                        |
| Body Appreciation Scale 2                                           | X                            |                              |                           | X                         | X                                      | X                                      |
| Body Image States Scale                                             | X                            |                              |                           | X                         | X                                      | X                                      |
| Body Shape Questionnaire                                            | X                            |                              |                           | X                         | X                                      | X                                      |
| EDE-Q Questionnaire                                                 | X                            |                              |                           | X                         | X                                      | X                                      |
| Exercise Addiction Inventory                                        | X                            |                              |                           | X                         | X                                      | X                                      |
| Appearance Anxiety Inventory                                        | X                            |                              |                           | X                         | X                                      | X                                      |
| Dysmorphic Concern Questionnaire                                    | X                            |                              |                           | X                         | X                                      | X                                      |
| EDI-3                                                               | X                            |                              |                           | X                         | X                                      | X                                      |
| Stunkard Figure Rating Scale                                        | X                            |                              |                           | X                         | X                                      | X                                      |
| Capsule rating scale pre-post intervention                          |                              | X                            |                           |                           |                                        |                                        |
| User experience rating scale                                        |                              | X                            |                           |                           |                                        |                                        |
| Photographic Figure Rating Scale pre/post intervention              | X                            | X                            |                           | X                         | X                                      | X                                      |
| PAGI-SYM Questionnaire                                              | X                            |                              | X                         | X                         | X                                      | X                                      |
| Meal Emotion Ratings                                                |                              |                              | X                         |                           |                                        |                                        |
| WHODAS 2.0 e                                             | X                            |                              |                           |                           |                                        |                                        |
| GAD-7 e                                                  | X                            |                              |                           |                           |                                        |                                        |
| DSM-5 Crosscutting assessment (adult) e                  | X                            |                              |                           |                           |                                        |                                        |
| DSM-5 Crosscutting assessment (youth self report) f      | X                            |                              |                           |                           |                                        |                                        |
| DSM-5 Crosscutting assessment (parent/guardian report) g | X                            |                              |                           |                           |                                        |                                        |
| RCADS-25 (youth self report) f                           | X                            |                              |                           |                           |                                        |                                        |
| RCADS-25 (parent/caregiver report) g                     | X                            |                              |                           |                           |                                        |                                        |
| Adverse event monitoring                                            | X-----X                      |                              |                           |                           |                                        |                                        |

aWomen of childbearing potential bState and trait version cAssessed via remote data collection, +/- 14 days dMay be self-reported

eParticipants 18 and older    fParticipants younger than 18    gParents of participants younger than 18    hCollected by inpatient staff  
iSTAI state version only

## **G. Human Participants**

We aim to recruit a total of 230 human subjects:

- 115 females with anorexia nervosa (AN), age 15 – 40 years.
- 115 healthy comparisons (HC), females, ages 15 – 40 years, who will be recruited to match to the AN sample based on age.

AN Inclusion criteria:

- i. Primary clinical diagnosis of anorexia nervosa as defined by Laureate Eating Disorders Program
- ii. Body mass index  $\geq 18.5$ . BMI cannot be below 18.5 within 1 week of capsule swallow.
- iii. Transitioned from acute clinical status rating to residential clinical status or partial/intensive outpatient clinical status rating
- iv. May be on SSRI and SNRI medications, as well as atypical antipsychotics, tricyclic antidepressants, buspirone, and lamotrigine.
- v. No new medication prescription in the week prior to study randomization, Must be on a stable dose of medication for at least 1 week.
- vi. Females, ages 15 to 40 years
- vii. Women of childbearing age: a hormonal (i.e., oral, implantable, or injectable) and single-barrier method, or a double-barrier method of birth control must be used throughout the study.
- viii. Independently ambulatory
- ix. Possession of a smartphone with data plan
- x. English proficiency
- xi. Willingness and ability to participate in study procedures
- xii. Provision of signed and dated informed consent form

AN Exclusion criteria:

- i. Active suicidal ideation with intent or plan
- ii. Active cutting or skin lacerating behaviors
- iii. Active purging behaviors (specifically, self-induced vomiting), and/or a history of severe self-induced vomiting
- iv. Pregnancy as defined by a urine screen during screening, and confirmed during each stimulation visit, and must not be lactating
- v. History of significant gastrointestinal disorder, including any form of inflammatory bowel disease or gastrointestinal malignancy (celiac disease is accepted if the subject has been treated and is in remission)
- vi. History of complicated/obstructive diverticular disease
- vii. Clinical evidence of significant gastroparesis
- viii. Diagnosis of mega-rectum or colon, congenital anorectal malformation, or clinically significant rectocele or rectal prolapse
- ix. History of intestinal or colonic obstruction, or suspected intestinal obstruction
- x. History of intestinal resection (with an exception for appendectomy, cholecystectomy and inguinal hernia repair), history of bariatric surgery or evidence of any structural abnormality of the gastrointestinal tract that might affect transit

- xi. History of Zenker's diverticulum, dysphagia, Barrett's esophagus, esophageal stricture or achalasia, transesophageal fistula, or eosinophilic esophagitis.
- xii. Clinical evidence (as judged by the investigator) of respiratory, cardiovascular, renal, hepatic, biliary, endocrine, or neurologic disease
- xiii. Chronic use of non-steroidal anti-inflammatory drugs (NSAIDs): chronic use is defined as taking full dose NSAIDs more than three times a week for at least six months. Subjects on cardiac doses of aspirin may be enrolled in the study
- xiv. Cardiac pacemaker, implantable cardioverter defibrillator, implantable infusion device, or gastric electrical stimulator
- xv. Orthostatic hypotension (defined as a drop of  $\geq 20$  mm Hg in systolic BP or a drop of  $\geq 10$  mm Hg in diastolic BP when measured shortly after transitioning from lying down to standing)
- xvi. Any other condition which in the opinion of the investigator may adversely affect the safety of the subject or would limit the subject's ability to complete the study
- xvii. No smartphone/computer or limited access to a smartphone/computer
- xviii. Regular use of any of the following medications or procedures: Medications that may substantially affect intestinal motility, prokinetics at high doses (metoclopramide, erythromycin, senna, prucalopride), anti-Parkinsonian medications, opiates, opioids, calcium-channel blockers, enemas
- xix. History of GI bleed within the last 3 months
- xx. Pelvic floor dysfunction/defecatory disorder, based on subject history
- xxi. Planning to undergo MRI during study time frame
- xxii. Any known allergy to soybean or beeswax, or Calcium Carbonate
- xxiii. Bradycardia less than 40 beats per minute
- xxiv. Pain Disorder

HC Inclusion criteria:

- i. Body mass index  $\geq 18.5$ . BMI cannot be below 18.5 within 1 week of capsule swallow.
- ii. Females, ages 15 to 40 years
- iii. Women of childbearing age: a hormonal (i.e., oral, implantable, or injectable) and single-barrier method, or a double-barrier method of birth control must be used throughout the study.
- iv. Independently ambulatory
- v. Possession of a smartphone with data plan
- vi. English proficiency
- vii. Willingness and ability to participate in study procedures
- viii. Provision of signed and dated informed consent form

HC Exclusion criteria:

- i. Current diagnosis of a psychiatric disorder per the MINI International Diagnostic Interview
- ii. Taking any psychotropic medication
- iii. Active suicidal ideation with intent or plan
- iv. Active cutting or skin lacerating behaviors
- v. Active purging behaviors (specifically, self-induced vomiting), and/or a history of severe self-induced vomiting
- vi. Pregnancy as defined by a urine screen during screening, and confirmed during each stimulation visit, and must not be lactating

- vii. History of significant gastrointestinal disorder, including any form of inflammatory bowel disease or gastrointestinal malignancy (celiac disease is accepted if the subject has been treated and is in remission)
- viii. History of complicated/obstructive diverticular disease
- ix. Clinical evidence of significant gastroparesis
- x. Diagnosis of mega-rectum or colon, congenital anorectal malformation, or clinically significant rectocele or rectal prolapse
- xi. History of intestinal or colonic obstruction, or suspected intestinal obstruction
- xii. History of intestinal resection (with an exception for appendectomy, cholecystectomy and inguinal hernia repair), history of bariatric surgery or evidence of any structural abnormality of the gastrointestinal tract that might affect transit
- xiii. History of Zenker's diverticulum, dysphagia, Barrett's esophagus, esophageal stricture or achalasia, transesophageal fistula, or eosinophilic esophagitis.
- xiv. Clinical evidence (as judged by the investigator) of respiratory, cardiovascular, renal, hepatic, biliary, endocrine, or neurologic disease
- xv. Chronic use of non-steroidal anti-inflammatory drugs (NSAIDs): chronic use is defined as taking full dose NSAIDs more than three times a week for at least six months. Subjects on cardiac doses of aspirin may be enrolled in the study
- xvi. Cardiac pacemaker, implantable cardioverter defibrillator, implantable infusion device, or gastric electrical stimulator
- xxv. Orthostatic hypotension (defined as a drop of  $\geq 20$  mm Hg in systolic BP or a drop of  $\geq 10$  mm Hg in diastolic BP when measured shortly after transitioning from lying down to standing)
- xxvi. Any other condition which in the opinion of the investigator may adversely affect the safety of the subject or would limit the subject's ability to complete the study
- xxvii. No smartphone/computer or limited access to a smartphone/computer
- xxviii. Regular use of any of the following medications or procedures: Medications that may substantially affect intestinal motility, prokinetics at high doses (metoclopramide, erythromycin, senna, prucalopride), anti-Parkinsonian medications, opiates, opioids, calcium-channel blockers, enemas
- xxix. History of a GI bleed within the last 3 months
- xxx. Pelvic floor dysfunction/defecatory disorder, based on subject history
- xxxi. Planning to undergo MRI during study time frame
- xxxii. Any known allergy to soybean or beeswax or Calcium Carbonate
- xxxiii. Bradycardia less than 40 beats per minute
- xxxiv. Pain Disorder

*Plans for recruitment and consent procedures to be followed:*

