**B. Background and Significance**

Anorexia nervosa (AN) has one of the highest mortality rates of any psychiatric illness (Arcelus et al., 2011), yet the pathophysiology of this disorder is poorly understood and current treatments show limited efficacy. Abnormalities of interoception, the brain-body connection, have been suggested to play a central role in manifestation of AN ([name] et al., 2018a), partly because of the phenotype of severe food restriction, ignoring of hunger signals, and extremely low body weight that characterize the disorder. However, few studies have rigorously examined the influence of interoception on illness expression in AN.

In our previous studies, we have demonstrated that individuals with AN show abnormal subjective awareness of interoceptive signals. For example, using the adrenaline analogue isoproterenol we found that individuals with AN report feeling cardiorespiratory sensations with greater intensity when anticipating eating a meal ([name] et al., 2015), an effect that was particularly pronounced for sensations of dyspnea. In a follow up study, we found that these patients were also more inaccurate at localizing cardiovascular sensations in the body, suggesting an impairment in the ability to accurately discriminate interoceptive signals occurring within the body ([name] et al., 2018b). These abnormalities are accompanied by evidence of abnormal activation in the insular cortex, a key hub for interoceptive processing in the brain (Hassanpour et al., 2018). For example, other studies have shown that current AN patients demonstrate greater insula activation than HC when attending to heartbeat sensations and lower insula activation to stomach sensations (Kerr et al., 2016), and recovered AN patients show experience greater choking sensations and show greater insula activation during an inspiratory breathing load paradigm (Berner et al., 2017).

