#### *Recruitment*

We plan to obtain measurements from 115 adult and teen inpatients with AN and 115 adult and teen healthy comparison participants over 5 years (see 'Human Participants' section for details). Participants will be recruited through a pre-approved LIBR Screening protocol (WIRB # 20200161, formerly 20101611), through the LIBR database, through flyers and social media advertisements, and through word of mouth via eating disorder clinicians at the Laureate Eating Disorders Program and in the community. In addition, teens will be recruited through local school districts using Peachjar (an online platform to deliver flyers to parents with information about afterschool activities).

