#### *Self-report assessments:*

Self-report measures may include demographics, measures of psychiatric health and eating disorder scales (see **Time and Events Table**).

*NIMH Data Archive (NDA) Common Data Elements:*

We are required to collect responses from participants to certain measures considered to be “common data elements” by the funding agency support this research (National Institute of Mental Health (NIMH) to submit to their NIMH Data Archive (NDA) as part of the funding agreement. These measures include the DSM-5 crosscutting assessment for adults, youth, and parents/guardians of youth; the WHODAS 2.0 and GAD-7 for adult participants; and the RCADS-25 for youth and parents/caregivers.

*Psychiatric and Medical History:*

All participants consenting to study will be asked to sign an authorization to release medical records from Laureate Psychiatric Clinic and Hospital.

*General Procedure*

Prior to starting the study, the experimenter will review the entire study procedure and informed consent document with the participant. Participants may be asked to complete a series of self-report questionnaires (see Time and Events Table) that will take between 1.5-2 hours to complete. These same measures may also be completed at the end of the study and during the follow up visit.

*Psychiatric and Medical Evaluations:*

Participants consenting to study entry may be asked a series of standardized questions about psychiatric or medical symptoms they have experienced during their lifetime, including a detailed medication history and family history. An unstructured psychiatric interview and a Structured Clinical Interview for DSM-IV Disorders (via the M.I.N.I. International Neuropsychiatric Interview (Sheehan et al., 1998)) may be administered as part of the determination of eligibility. These assessments will be obtained through the LIBR Screening protocol. All participants will undergo a physical exam including measurement of vital signs, taking a breathalyzer test, and submission of urine sample for pregnancy and drug screening. During this visit many of the self report assessments may be completed. This visit may be conducted over a period of up to 14 days.

*Sensation and emotion measurement:*

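### Healthy comparisons are screened for current psychiatric diagnosis but not for a past eating disorder, so some women recovered from AN could enter the control group and weaken the hypothesised Aim 1 differences

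*Protocol*

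**What the plan says.** Section G sets the HC eligibility rules. The psychiatric exclusion is "Current diagnosis of a psychiatric disorder per the MINI International Diagnostic Interview". Two further HC exclusions bear on past illness: "Taking any psychotropic medication" and "Active purging behaviors (specifically, self-induced vomiting), and/or a history of severe self-induced vomiting". The minimum BMI of 18.5 is the same for HCs and for the AN group. The investigator-judgement exclusion is limited to the participant's safety and ability to complete the study.

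Section D, under Psychiatric and Medical Evaluations, allows that participants may be asked a "series of standardized questions about psychiatric or medical symptoms they have experienced during their lifetime". It says the interviews, including the MINI, "may be administered as part of the determination of eligibility". No HC criterion refers to that lifetime history.

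Section B, on earlier work, states that "recovered AN patients show experience greater choking sensations and show greater insula activation" in a breathing-load task.

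Hypothesis 1a expects lower interoceptive precision (IP), stronger prior expectations (pGI) and a lower learning rate in AN than in HC. Hypothesis 1b expects a smaller evoked brain response in AN but equal gastric myoelectric (EGG) responses.

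**The concern.** The HC group is the reference for Aim 1. If it contains women who once had AN, and if they keep part of the interoceptive trait under study, the two groups are less different than the design assumes. The bias in IP, pGI, learning rate and ERP is toward zero, so a real difference may be missed or understated.

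EGG works differently. The expected result there is no difference, and the top-down reading of Aim 1 rests partly on it. If AN did alter EGG and recovered women shared the alteration, their presence among the controls would help produce the expected null.

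BMI cannot separate such women from other controls, because the AN group is itself weight-restored to at least 18.5. The protocol does use lifetime wording elsewhere in the same list, for gastrointestinal disease, obstruction, resection and severe vomiting. The psychiatric criterion is limited to the present.

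**Working it through.** **1. Can a recovered woman qualify?** Take a woman with past restricting-type AN, now with BMI at least 18.5, on no psychotropic medication, with no current diagnosis and no history of severe vomiting, and meeting the general medical criteria.

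- Current psychiatric diagnosis: none, so not excluded.
- Medication: none, so not excluded.
- Purging or severe vomiting history: none, so not excluded.
- Investigator judgement: a past eating disorder is not in itself a matter of safety or of ability to complete.
- Lifetime history: possibly recorded, but tied to no exclusion.

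She qualifies as a healthy comparison.

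**2. The plan's own sample size.** Section E uses 25% in AN, 5% in HC, 95% power and alpha 0.05, and obtains 65 completers per group. The sidedness of the test is not stated. One-sided with pooled variance:

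n = [1.645·√(2·0.15·0.85) + 1.645·√(0.25·0.75 + 0.05·0.95)]² / 0.20² = (0.831 + 0.797)² / 0.04 ≈ 66.3, so 67 per group.

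The unpooled version gives 64. The stated 65 is therefore reproduced to within two per group as a one-sided test (two-sided needs 80). That calculation concerns relapse against HC expression of eating psychopathology. The protocol sizes no Aim 1 outcome and says no earlier effect sizes exist for this assay.

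**3. Dilution of a continuous Aim 1 contrast.** Assumptions, none of them given in the protocol:

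- True standardised difference d = 0.5.
- A share f of HCs has a past eating disorder.
- Those women carry the whole AN effect (worst case).

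The observed difference is then d(1 − f), and two-sided power is Φ(d(1 − f)·√(n/2) − 1.96). With n = 65, √(n/2) = 5.701.

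| f | d(1 − f) | d(1 − f)·5.701 − 1.96 | Power, 65 per group |
|---|---|---|---|
| 0% | 0.500 | 0.890 | 81.3% |
| 2% | 0.490 | 0.833 | 79.8% |
| 5% | 0.475 | 0.748 | 77.3% |
| 10% | 0.450 | 0.605 | 72.8% |
| 20% | 0.400 | 0.320 | 62.6% |

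With the t distribution in place of the normal, the figures at 0%, 5% and 10% are 80.8%, 76.7% and 72.1%. If 115 are recruited per group and 20% are lost, 115 × 0.80 = 92 remain. Power on the normal formula is then 92.4% at f = 0, 89.6% at 5% and 86.3% at 10%.

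**4. The same assumption applied to the plan's proportions.** If affected HCs had the AN event rate, the HC rate would be 0.05 + 0.20f. One-sided power at 65 per group would go from 94.7% (f = 0) to 93.6% (2%), 91.9% (5%) and 88.3% (10%). This too is a ceiling on the loss.

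**The case against.** **The evidence on recovered patients is indirect.** The finding cited in Section B is that they "show greater insula activation during an inspiratory breathing load paradigm". That is a respiratory task with greater activation. Hypothesis 1b expects a smaller response to gastric stimulation, and Section B itself reports lower insula activation to stomach sensations in current AN. Section B also says gastrointestinal symptoms fall substantially in the six months after inpatient care, which suggests at least partial normalisation. This objection stands as a limit on size: full carry-over is a worst case. It does not make recovered women a sound healthy reference.

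**Other criteria already remove part of this population, and the share left may be small.** This also stands. At 2% the worst-case loss is 1.5 percentage points, which is negligible.

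**A reader might infer that every AN-HC comparison is diluted.** The protocol does not support that. EGG is expected to be equal, and the Aim 2 hypotheses concern outcome and severity within AN.

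**A reader might infer that eating-disorder clinicians will channel recovered women into the HC group.** Section D does list recruitment "through word of mouth via eating disorder clinicians at the Laureate Eating Disorders Program and in the community", but without splitting by group. The recruitment text in Section G assigns clinician referral to AN and gives other routes for HCs. The two texts should be reconciled; they do not show a raised risk.

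**The bias is toward the null, so it cannot manufacture an AN-HC difference.** This is true for the contrasts expected to differ. It is no reassurance for EGG, where the null is the prediction.

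**Conclusion.** The gap holds and is worth closing. As written, the HC criteria admit an unmedicated woman recovered from an eating disorder who has no history of severe vomiting. The contrasts at risk are the hypothesised AN-HC differences in IP, pGI, learning rate and ERP (bias toward zero) and EGG (bias toward the expected null).

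The size is unknown because the protocol gives no share. The power figures are upper bounds on the loss and rest on an assumed d of 0.5 and full carry-over of the AN trait. On that basis the loss at 65 per group runs from nothing at 0% to about 4 percentage points at 5% and 8 to 9 at 10%.

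A reader might go further and call the sample size invalid or the controls contaminated in fact. The protocol supports neither: it says nothing about how many such women will enrol. Its 5% HC rate concerns eating psychopathology during the study period, not past illness. This is a weakness in an eligibility rule, not an arithmetic error.

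**What to change.** 1. Add a lifetime history of any eating disorder to the HC exclusions in Section G.
2. Make the lifetime psychiatric history in Section D mandatory for HCs. Section D now leaves it, and the MINI, optional, so the new exclusion could not otherwise be applied reliably.
3. For HCs already enrolled, establish that history and run the Aim 1 analyses with and without those who have a past eating disorder. Include EGG, and state this before group data are examined.
4. Reconcile the two recruitment texts (Sections D and G) so that the routes for each group are clear.

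The cost is a short amendment, somewhat more history-taking where it is not already done, and the loss of a few otherwise eligible HCs. If past eating disorders prove to be absent or very rare among enrolled HCs, the sensitivity analysis will show that and the issue closes.
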